#### Data management and quality control

2.3.4

To ensure data quality, all research personnel will undergo standardized training prior to study initiation. Training will cover patient recruitment, data collection procedures, biological sample handling, and electronic data entry. Only personnel who pass the qualification examination will be authorized to participate in the research.

A two-level quality control system will be implemented:

Level-I quality control will be conducted by site coordinators who will review completed questionnaires, verify data accuracy against source documents, and ensure proper biological sample collection.Level-II quality control will be performed by the central coordinating team through regular site visits, random sampling of 10% of data for source verification, and identification of potential data inconsistencies.

All data will be entered into a dedicated electronic data capture (EDC) system with built-in logic checks to identify potential errors or inconsistencies. The system will generate data queries that must be resolved before data can be considered final.

Biological samples will be managed through a standardized coding system that ensures patient confidentiality while maintaining traceability. All samples will be stored in a dedicated biobank at -80 °C, with limited access and regular inventory checks to ensure sample integrity.

#### Outcomes

2.3.5

The primary outcomes of this prospective multicenter cohort study comprise two main endpoints: CRC occurence and CRA recurrence is defined as any histologically confirmed CRA detected during scheduled follow-up colonoscopy examinations at 12, 24, 36, 48, and 60 months after baseline. Each adenoma will be systematically evaluated according to standardized criteria, including anatomical location within the colorectum, maximum diameter measured by open biopsy forceps, and total number of lesions. Histological classification will follow the World Health Organization criteria.

For CRC occurence, the outcome is defined as any histologically confirmed CRC diagnosed during the follow-up period. Each case will undergo comprehensive assessment including TNM staging classification according to the American Joint Committee on Cancer (AJCC) 8th edition, detailed histological type and grade evaluation, and precise documentation of tumor location and size. To ensure data quality and consistency, all colonoscopy procedures will be performed by certified endoscopists following standardized protocols, and all pathological specimens will undergo centralized review by experienced gastrointestinal pathologists.

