Baseline TCM diagnostic information (tongue appearance, pulse characteristics, and symptomatic manifestations) will be collected simultaneously by trained research personnel. Collection timing will be strictly standardized to 24–48 hours post-admission and prior to colonoscopy, exclusively during morning fasting state (8-hour food restriction, 2-hour fluid restriction) to eliminate temporary interference from dietary intake or endoscopic procedures. This observational study will enroll only patients with first-time CRA detection (confirmed through comprehensive history review and colonoscopy of no previous adenoma history). At baseline, participants will receive no adenoma-specific treatments (including oral Chinese herbal medicine, herbal enemas, or other TCM interventions). During hospitalization (mean duration ≤1 week), patients will receive only routine Western medications related to surgical procedures (e.g., bowel preparation agents), ensuring baseline TCM diagnostic data accurately reflected the pathological status. Post-discharge self-administration of Chinese herbal medications is possible; this aspect will be systematically monitored during the follow-up period.

Clinical data collection will focus on comprehensive documentation of adenoma characteristics through colonoscopy and pathological examination. Colonoscopy findings will include the number, size, location, and morphological features of adenomas. Pathological assessment will document adenoma type (tubular, tubulovillous, villous), degree of dysplasia, and margin status. These parameters are essential for risk stratification of patients and determination of appropriate surveillance intervals.

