#### Follow-up schedule and procedures

2.3.3

Follow-up examinations will be conducted at 12, 24, 36, 48, and 60 months after enrollment. During each follow-up visit:

Clinical examination encompassed comprehensive history-taking (with emphasis on gastrointestinal symptoms and treatment-related complications) and thorough physical examination. Follow-up assessments utilized structured questionnaires combined with medication verification to document patients’ TCM usage over the preceding 6 months, recorded in the ‘Follow-up Medication Record Form’ For patients reporting TCM use, TCM diagnostic data collection was immediately suspended, and patients were instructed to discontinue all TCM preparations for 1 week before returning for morning fasting reassessment. This protocol enabled dual verification through baseline-versus-follow-up data comparison and post-cessation sign monitoring, allowing differentiation between treatment-induced changes and genuine pathological manifestations.Colonoscopy will be performed according to standard clinical practices to detect adenoma recurrence (**Table 2**). The timing and frequency may be adjusted based on baseline findings according to guidelines for adenoma surveillance (14, 15).Updated laboratory tests similar to baseline will be performed to monitor changes and identify potential biomarkers of adenoma recurrence or progression.TCM syndrome evaluation will be repeated to track changes in syndrome patterns and their potential association with disease progression.Risk factor assessment will be updated, including changes in lifestyle factors (smoking, alcohol consumption, diet, physical activity).Treatment information will be collected, documenting both Western medical interventions and TCM treatments.

**Table 2 T2:** Follow-up intervals after endoscopic resection of colorectal polyps or adenomas.

Initial colonoscopy findings	Colonoscopy follow-up interval (Years)
No polyps	3–5
Hyperplastic polyp in rectum or sigmoid(diameter <10 mm)	2–3
1–2 tubular adenomas (diameter < 10 mm)	1–3
3–10 tubular adenomas	1–2
≥ 1 tubular adenoma (diameter ≥ 10 mm)	1–2
≥ 1 villous adenoma	1–2
Adenoma with high-grade intraepithelial neoplasia	1–2
Serrated lesion < 10 mm without intraepithelial neoplasia	2–3
Serrated lesion > 10 mm without intraepithelial neoplasia	1–2

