In cases of special circumstances such as new symptoms (hematochezia, change in bowel habits, unexplained weight loss), additional examinations including earlier colonoscopy, enhanced CT, or MRI may be performed outside the scheduled follow-up timepoints, with these events recorded in detail.

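### CRA recurrence counts only adenomas found at scheduled colonoscopies, and the protocol gives two colonoscopy schedules, one of which would tie detection time to baseline findings

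*Protocol article*

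**What the plan says.** **Outcome definition.** Section 2.3.5 defines CRA recurrence, a primary outcome, as "any histologically confirmed CRA detected during scheduled follow-up colonoscopy examinations at 12, 24, 36, 48, and 60 months after baseline". For the other primary outcome, CRC, "the outcome is defined as any histologically confirmed CRC diagnosed during the follow-up period", with no link to a scheduled visit.

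**Off-schedule examinations.** Section 2.3.3 provides that for "new symptoms (hematochezia, change in bowel habits, unexplained weight loss), additional examinations including earlier colonoscopy" and imaging "may be performed outside the scheduled follow-up timepoints, with these events recorded in detail". Nothing says whether an adenoma found at such an examination counts. Section 2.3.5 adds that "all pathological specimens will undergo centralized review by experienced gastrointestinal pathologists".

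**Schedule.** Table 1 ticks colonoscopy at all five annual visits, matching the months in 2.3.5. The Abstract, however, calls the intervals risk-stratified. Section 2.3.2 says of the baseline adenoma features: "These parameters are essential for risk stratification of patients and determination of appropriate surveillance intervals". Section 2.3.3 says of colonoscopy: "The timing and frequency may be adjusted based on baseline findings according to guidelines for adenoma surveillance". Table 2 gives 1-3 years for one or two small tubular adenomas and 1-2 years for the higher-risk adenoma rows.

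**Analysis.** Section 2.3.10 names Kaplan-Meier for cumulative incidence and Cox regression for risk factors, with subgroups that include baseline adenoma characteristics.

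**The concern.** There are two linked problems, resting on different text.

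1. The recurrence definition leaves out events that the study will observe, record and review. A patient whose adenoma is removed at a symptom-driven colonoscopy can be clear at the next scheduled visit and be analysed as recurrence-free. The recurrence estimate is then too low by an amount nobody has set.

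2. Recurrence is seen only when someone looks. If baseline findings decide how often that happens, the same adenoma is dated earlier in a patient examined more often. A baseline finding with no effect on recurrence can then show a hazard ratio away from 1. Baseline adenoma findings are subgroup variables and natural candidates for the planned prediction model, so this would touch a stated objective.

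**Working it through.** **The plan's own figures (2.3.6).** The formula is N = (1.96 + 1.28)² × P(1−P)/d².
- Recurrence, P = 0.58, d = 0.02: 10.4976 × 0.2436 / 0.0004 = 6,393.04, rounded up to 6,394 as stated. 6,394/0.8 = 7,992.5, so 7,993 as stated.
- CRC, P = 0.0035, d = 0.00175: 11,956 against 11,970 stated, a 0.1% difference. 11,970/0.8 = 14,962.5, so 14,963. This figure sets the 15,000 target.

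**Part 1: events lost by the definition.** Let P be 5-year recurrence, f the share of recurrences first found off schedule, and r the chance of a further adenoma at a later scheduled look. The fall in the estimate is P × f × (1−r). The protocol gives P = 48%-68% (midpoint 58%) and a 2-point absolute error. It gives neither f nor r, so both are assumptions.
- f giving a 2-point fall at P = 58%: 0.02/0.58 = 3.4% (r = 0); 0.02/(0.58 × 0.5) = 6.9% (r = 0.5).
- f = 5%, P = 58%: 0.58 × 0.05 = 2.9 points (r = 0), or 1.45 points (r = 0.5).
- f = 5%, P = 48% to 68%: 2.4 to 3.4 points (r = 0), or 1.2 to 1.7 points (r = 0.5).

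**Part 2: unequal schedules under equal true risk.** Inputs from 2.3.6 are 15%-30% recurrence at 3 years and 58% at 5 years. I used a piecewise-constant hazard with a break at 3 years. With 22.5% at 3 years, the yearly hazard is −ln(0.775)/3 = 0.085 up to year 3, then [ln(0.775) − ln(0.42)]/2 = 0.306. The 15% and 30% cases follow the same way.

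The remaining choices are assumptions: event time is the date of the first positive colonoscopy, follow-up ends at the last colonoscopy, and Cox is fitted to expected data with Efron ties. The true hazard ratio is 1 throughout. Ratios are for the first-named group; ranges run over the three 3-year rates and over 25%, 50% and 75% of patients in the second group.

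Extreme contrasts, each group held entirely to one schedule (looks in years):

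| First group | Second group | Spurious HR |
|---|---|---|
| 1, 2, 3, 4, 5 | 2, 4 | 1.03-1.07 |
| 1, 2, 3, 4, 5 | 2, 4, 5 | 1.02-1.05 |
| 1, 2, 3, 4, 5 | 3 | 1.06-1.13 |
| 1, 2, 3, 4, 5 | 3, 5 | 1.14-1.17 |
| 2, 4 | 3 | 0.71-0.78 |
| 2, 4, 5 | 3, 5 | 1.11-1.17 |

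Table 2 ranges overlap, so a mix is more realistic. As an illustration, put higher-risk patients half on annual and half on 2-yearly looks, and lower-risk patients one third each on annual, 2-yearly and 3-yearly looks.
- With a month-60 look (2, 4, 5 and 3, 5): HR 1.04-1.06.
- Without it (2, 4 and 3): HR about 0.99.
- Everyone annual: HR 1, no distortion.

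**Check of the remedy.** An interval-censored proportional hazards model was fitted to simulated data on fixed schedules (22.5% at 3 years, 400 runs per design). It gave mean hazard ratios of 0.999-1.000 and rejected at P<0.05 in 2.8%-7.2% of runs. Symptom-driven looks were not part of that check.

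**The case against.** **Scheduled-only counting can be deliberate.** It keeps extra looks in symptomatic patients from inflating recurrence. That aim is legitimate, but the article does not state it, and a sensitivity analysis serves it without discarding events. The off-schedule data are recorded either way, so the loss lies in the definition and not in data collection.

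**Annual colonoscopy for all may be what is meant.** Table 1 and 2.3.5 say so, 2.3.3 says only that timing may be adjusted, and one year lies within every adenoma row of Table 2. If annual examination is carried out, part 2 disappears. What stands is that the article describes both schedules.

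**Event-date and censoring rules belong to an analysis plan.** Their absence is not a fault, and part 2 is therefore conditional. The article does, however, name Kaplan-Meier and Cox alongside intervals set by baseline findings.

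**Readings that go too far.** A reader might infer that a null baseline finding would almost surely come out significant. In simulations with 6,000 patients per group, annual looks against looks at years 3 and 5 rejected in all runs. That requires each group to be held wholly to one schedule, which Table 2 does not prescribe. The sizes also depend on the hazard shape: a constant hazard gives 1.10 (annual against 2-yearly), 1.20 (annual against 3-yearly) and 0.82 (2- against 3-yearly), though it implies about 41% recurrence at 3 years, outside the protocol's 15%-30%. A reader might also infer that lost recurrences differ by TCM syndrome, or that the sample size is undermined. The document has nothing to show the first. The second is wrong, because recurrence needs 7,993 patients against a target of 15,000.

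**Conclusion.** Both parts hold, with different certainty.

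Part 1 follows directly from the text: a primary outcome excludes adenomas found at examinations that the protocol itself provides for, while the companion outcome has no such limit. Its size is unknown. A loss of 3.4% to 6.9% of recurrences would equal the planned 2-point error at 58% recurrence.

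Part 2 is a certain inconsistency over the schedule and a conditional bias. If intervals do differ and detection date is the event time, a modest spurious hazard ratio of about 1.04-1.06 is plausible under the illustrative mix with a month-60 look, and about 0.99 without that look. The range 0.71-1.17 marks extreme contrasts under the protocol's rates, and its direction depends on the sequence of looks. These figures illustrate the effect; they do not estimate it. The matter should be fixed before analysis, but it does not threaten the study's size or feasibility.

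**What to change.** 1. Define CRA recurrence as any histologically confirmed CRA found at any colonoscopy after the baseline clearing colonoscopy, whether scheduled or symptom-driven.
2. Record the date and the reason for every colonoscopy.
3. Add a sensitivity analysis that assigns each off-schedule adenoma to the next scheduled date, or that uses scheduled examinations only.
4. Make Table 1, section 2.3.5 and Table 2 state one schedule, without dropping colonoscopies already planned. Relaxing Table 1 to the Table 2 ranges would be the wrong direction: it would remove annual examinations and create the unequal schedules at issue.
5. Analyse recurrence with an interval-censored proportional hazards model, from last clear to first positive colonoscopy, with follow-up ending at the last colonoscopy. Standard versions assume that examination times are unrelated to the event, which symptom-driven looks can violate. The analysis in item 3 is the check on that.

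**Cost.** One definition sentence, consistent schedule wording, an eCRF field for the reason, one sensitivity analysis and a different recurrence model. No colonoscopies are added or removed, and the events, specimens and reports are already captured. The downsides are a slightly more complex analysis and the chance that some early detections are lesions missed at baseline.

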#### Sample size

2.3.6

For this multicenter prospective cohort study, we calculated the sample size based on two primary outcomes: CRA recurrence and CRC occurrence. According to previous studies, the detection rate of CRA ranges from 15%-30% during 3-year follow-up and reaches 48%-68% during 5-year follow-up, while the annual incidence of CRC among adenoma patients is approximately 0.2%-0.5%.

We employed the cohort study sample size calculation formula N = (Zα/2 + Zβ)² × P(1-P)/d², where Zα/2 = 1.96 (α = 0.05, two-sided), Zβ = 1.28 (statistical power = 90%), and d represents the acceptable margin of error. Two primary outcomes guided our sample size determination: CRA recurrence and malignant transformation.

For the adenoma recurrence outcome, we considered the 5-year cumulative recurrence rate ranging from 48% to 68%, with a median of 58%. Using an absolute error of 2%, the minimum sample size calculation yielded 6,394 cases. After accounting for a 20% potential loss to follow-up, the adjusted sample size was 7,993 cases.

Regarding malignant transformation, the occurrence rate was estimated between 0.2% and 0.5%, with a median of 0.35%. We applied a relative error of 50% (0.175%), which resulted in a minimum sample size of 11,970 cases. Incorporating the 20% follow-up loss adjustment, the final target became 14,963 cases.

Considering the statistical requirements, research resources, and the need for robust analysis, we ultimately set the total enrollment target at 15,000 participants. This approach ensures adequate statistical power to detect clinically meaningful differences while providing comprehensive insights into CRA progression and cancer risk. This sample size ensures adequate statistical power to detect clinically meaningful differences in both primary outcomes while accounting for potential loss to follow-up. An interim analysis will be conducted when 50% of the target sample size is achieved.

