## Abstract

**Introduction:**

Colorectal adenoma (CRA), the main precursor of colorectal cancer (CRC), has a high recurrence rate (5-year cumulative: 48 - 68%) and a malignant transformation risk (0.2 - 0.5%). Traditional Chinese Medicine (TCM) provides a potential method to improve risk assessment and prevention. Based on TCM theories and the characteristics of colorectal adenoma, we hypothesize that an integrated system combining TCM syndromes, constitution types, and modern medical parameters can better predict adenoma recurrence and CRC occurrence.

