## Introduction

1

Colorectal adenoma (CRA), characterized by abnormal proliferation of colorectal mucosal epithelium, represents the most significant precancerous lesion for colorectal cancer (CRC) (1). Global data indicate that the 5-year cumulative recurrence rate after adenoma resection reaches 48%-68%, with approximately 0.2%-0.5% progressing to malignancy (2). In China, with the widespread adoption of endoscopic screening, the detection rate of CRA has been steadily increasing (3). Both domestic and international guidelines consider that the current optimal treatment for CRA is endoscopic resection, which can significantly reduce the incidence of CRC (1–4). Expert consensus on endoscopic diagnosis and treatment for colorectal cancer and precancerous lesions in China (2023, Guangzhou) states that for colorectal adenomatous polyps or polyps with a long diameter ≥5 mm, endoscopic resection is recommended, and the follow-up interval should be comprehensively determined based on factors such as pathological nature, lesion size, and number (1). The European Society of Gastrointestinal Endoscopy (ESGE) guidelines and the National Comprehensive Cancer Network (NCCN) guidelines, on the other hand, suggest that different endoscopic treatment methods can be selected according to the different types of polyps (3, 4). While risk factors for CRA have been studied, with pathological diagnosis as the gold standard and endoscopic resection as the primary intervention, large-scale cohort studies are still needed for further validation (4). TCM has shown promise in the diagnosis and prevention of adenoma recurrence, though more evidence is needed to support its clinical efficacy and mechanisms (5).

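### The CRC rate behind the larger sample-size requirement is called annual, then used with no time unit as the risk over the whole 5-year follow-up

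*Protocol article*

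**What the plan says.** Section 2.3.6 (Sample size) opens with the rates taken from previous studies. For cancer it says "while the annual incidence of CRC among adenoma patients is approximately 0.2%-0.5" per cent. It then gives the formula "N = (Zα/2 + Zβ)² × P(1-P)/d²". After the recurrence calculation comes the one for malignant transformation: "the occurrence rate was estimated between 0.2% and 0.5%, with a median of 0.35" per cent. This time there is no time unit. The margin follows: "We applied a relative error of 50% (0.175" per cent. The results are 11,970, and 14,963 after 20% loss to follow-up.

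Elsewhere the same range appears without a per-year label. The Introduction (section 1) has "with approximately 0.2%-0.5% progressing to malignancy", in the same sentence as the 5-year cumulative recurrence rate. The Abstract has "a malignant transformation risk (0.2 - 0.5" per cent.

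Three other statements bear on the time base:
- Section 2.3.5 (Outcomes) counts any confirmed CRC found over the follow-up, and the Abstract sets follow-up at 5 years.
- The recurrence calculation in section 2.3.6 uses an explicitly 5-year cumulative rate (midpoint 58%) and gives 6,394, or 7,993 after loss.
- The enrolment target is 15,000.

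**The concern.** The formula has no follow-up term, so P must be the proportion with the outcome over whatever window the outcome covers. For CRC, section 2.3.5 makes that window the whole follow-up. A yearly rate cannot be entered there unchanged, and a whole-study risk should not be labelled annual. One of the two statements in section 2.3.6 therefore needs correcting.

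This matters because CRC gives the larger of the two requirements (14,963 against 7,993), and 15,000 sits just above it. The time base also changes the expected number of CRC events about five-fold. CRC is a primary outcome with Cox, competing-risk and subgroup analyses planned in section 2.3.10, so a reader needs that count to judge how much those analyses can carry. The article does not give it.

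**Working it through.** **Inputs (section 2.3.6 unless noted).** "Zα/2 = 1.96 (α = 0.05, two-sided"); "Zβ = 1.28 (statistical power = 90" per cent); P = 0.35%, the midpoint of 0.2% to 0.5%; d = 50% of P = 0.175 percentage points; loss 20%, applied as N/0.8; follow-up 5 years (Abstract). The formula is taken as the article gives it.

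**1. Reproduce the plan's figures.**
- (1.96 + 1.28)² = 10.4976.
- CRC: 10.4976 × 0.0035 × 0.9965 / 0.00175² = 11,955. With unrounded normal quantiles it is 11,966. The stated 11,970 agrees to within rounding, and 11,970 / 0.8 = 14,963 as stated.
- Recurrence: 10.4976 × 0.58 × 0.42 / 0.02² = 6,393.04, rounded up to 6,394; 6,394 / 0.8 = 7,993. Both match.

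So the stated CRC figures come from P = 0.35% as it stands, with no conversion from a yearly rate.

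**2. If 0.35% is the risk over the whole study.** The requirement stands. Expected CRCs are:
- 12,000 completers (15,000 × 0.8): 12,000 × 0.0035 = 42, with 24 at 0.2% and 60 at 0.5%.
- All 15,000 followed: 52.5, about 53.

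**3. If 0.35% is annual, with constant risk.** The 5-year risk is 1 − (1 − 0.0035)⁵ = 1.74%. At 0.2% and 0.5% a year it is 0.996% and 2.475%. Expected CRCs are:
- 12,000 completers: about 209, with a range of 120 to 297.
- All 15,000 followed: about 261.

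**4. The CRC requirement on the annual reading depends on which form of the margin is kept.**

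| Margin kept | d at P = 1.74% | N | N / 0.8 |
|---|---|---|---|
| 50% relative (as labelled) | 0.87 points | 2,374 | 2,968 |
| 0.175 points absolute | 0.175 points | about 58,500 | about 73,200 |

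With the relative margin, the after-loss figure runs from 5,217 (0.2% a year) to 2,068 (0.5% a year). All of these lie below the 7,993 for recurrence.

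**5. Precision delivered.** The 95% half-width among 12,000 completers is 1.96 × √(P(1 − P)/12,000). At P = 0.35% this is 0.106 points, about 30% of P. At P = 1.74% it is 0.234 points, about 13% of P.

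**The case against.** The strongest defence is that nothing has been shown to be miscalculated. The article never writes *5-year* or *cumulative* beside 0.35%; that reading is inferred from the formula, the outcome definition and the parallel recurrence calculation. If *annual* is a slip, one word changes and 11,970 and 14,963 stand. This is correct: the fault is an undefined time base, not faulty arithmetic.

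It could also be said that the authors sized for the precision of a one-year incidence. The text does not expressly exclude this, but it gives it little support. No one-year CRC outcome is stated, and the loss applied is the same 20% used for the 5-year recurrence outcome.

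A reader might also infer that the trial is wrongly sized. The documents do not support that. At the midpoint rate and the stated relative margin, 15,000 exceeds 14,963 on one reading, and exceeds both 2,968 and 7,993 on the other. Nor does the target rest on CRC alone: section 2.3.6 also cites resources and the need for robust analysis, and section 2.3.10 defends 15,000 by syndrome counts.

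Finally, a reader might infer that the time unit decides whether any CRC analysis is possible. The documents set no event threshold. About 42 events would limit how complex a model can be, but would not rule out every analysis.

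**Conclusion.** The point holds as an internal contradiction in the input to the larger sample-size requirement. The stated 11,970 and 14,963 are consistent only with 0.35% as a whole-study risk, and section 2.3.6 itself calls that range annual. The documents do not settle which was intended.

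Expected CRC events differ by a factor of about 5.0 (209 / 42). The effect on N has no single direction. It falls about five-fold if the relative margin is kept, which makes recurrence the larger requirement, and rises about five-fold if the absolute margin is kept. Because the article labels the margin as relative, the fall is the more natural consequence of the annual reading, but it is conditional on that choice.

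The event counts assume constant yearly risk where the rate is read as annual. The counts at 12,000 also credit no events to the 20% lost, although the planned Kaplan-Meier and Cox analyses would use their observed time. The counts at 15,000 assume complete follow-up. They are planning figures, not exact expectations.

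**What to change.** State one time base for the CRC rate and use it in the Abstract, the Introduction and section 2.3.6. Then make one of two corrections:

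- **If 0.2% to 0.5% is the 5-year risk:** delete *annual*, say 5-year where the range appears, and leave 11,970 and 14,963 as they are.
- **If it is annual:** replace P with the 5-year risk (about 1.74% under constant risk), state whether the margin is 50% relative or 0.175 points absolute, recompute the CRC requirement, and say which outcome is now the larger requirement.

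In either case keep enrolment at 15,000. Add a sentence giving the expected CRC count and the precision it delivers, with the assumptions behind them (completers or all enrolled; constant risk).

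The cost is rewording one paragraph, aligning two others and, on the annual reading, recomputing the two CRC figures. Recruitment, visits and data collection do not change.

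### The sample-size formula adds a 90% power term to a quantity defined as a margin of error, so the stated minimum sizes are larger than the stated errors require

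*Protocol article*

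**What the plan says.** The calculation is in section 2.3.6 (Sample size) of the protocol article: "We employed the cohort study sample size calculation formula N = (Zα/2 + Zβ)² × P(1-P)/d²". The first constant is the usual value for a two-sided 5% level, 1.96. The power term and the meaning of d are given as "Zβ = 1.28 (statistical power = 90%), and d represents the acceptable margin of error".

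- Adenoma recurrence: the planning rate is 58%, the middle of a 48% to 68% range over 5 years. The size is given as follows: "Using an absolute error of 2%, the minimum sample size calculation yielded 6,394 cases". Allowing for 20% loss, the plan raises this to 7,993.
- Colorectal cancer: the planning rate is 0.35%, the middle of a 0.2% to 0.5% range. The size is given as follows: "We applied a relative error of 50% (0.175%), which resulted in a minimum sample size of 11,970 cases". The same 20% allowance raises this to 14,963, and the target is then set at 15,000.

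The section closes by saying, twice, that this size gives enough power to detect meaningful differences. It names no reference rate, no groups to compare and no size of difference.

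**The concern.** Two kinds of calculation are mixed. A margin of error is the half-width of a confidence interval and depends on Zα/2 only. Power belongs to a test, which needs a reference value or a second group. Here d is called a margin of error, and then an absolute or relative error, yet the multiplier is one for a test at 90% power.

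Two things follow. The minimum sizes do not correspond to the errors they are paired with. The section also appears to support a power claim although no comparison was sized. The cancer calculation yields 14,963, the computed figure closest to the 15,000 target, so the main numerical support for the target does not mean what it says.

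**Working it through.** **Inputs, all from section 2.3.6.** Zα/2 = 1.96; Zβ = 1.28. Recurrence: P = 0.58, d = 0.02. Cancer: P = 0.0035, d = 0.00175. Loss to follow-up 20%; enrolment 15,000.

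**Step 1. Reproduce the plan's figures.** N = (1.96 + 1.28)² × P(1−P)/d², with 3.24² = 10.4976.

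- Recurrence: 10.4976 × 0.2436 / 0.0004 = 6,393.0 (stated 6,394). 6,394/0.8 gives 7,993, as stated.
- Cancer: 10.4976 × 0.00348775 / 0.0000030625 = 11,955.3 (stated 11,970). 11,970/0.8 gives 14,963, as stated. The 0.1% gap is rounding of Zβ: 1.282 gives 11,970.

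One-sided alpha (5,216 and 9,753) or 80% power (4,780 and 8,939) does not reproduce the figures, so the 90% power term was used.

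**Step 2. Size for the stated errors.** N = 1.96² × P(1−P)/d², with 1.96² = 3.8416.

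- Recurrence: 3.8416 × 0.2436 / 0.0004 = 2,339.5, so 2,340; 2,340/0.8 = 2,925.
- Cancer: 3.8416 × 0.00348775 / 0.0000030625 = 4,375.03, so 4,376; 4,376/0.8 = 5,470.

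The inflation factor is 10.4976/3.8416 = 2.73 for both.

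**Step 3. Exact limits for the rare outcome.** 4,376 × 0.0035 is about 15 events, where the normal approximation is poor. With Clopper-Pearson limits at 0.35%:

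- half the interval width comes within 50% of the rate at 18 events in 5,143 patients (49.3%), but not at 17 in 4,857 (50.8%);
- the upper limit comes within 50% at 23 events in 6,571 (49.9%), but not at 22 in 6,286 (51.3%).

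About 5,100 to 6,600 are therefore needed, and the excess is 11,970/5,143 = 2.3 down to 11,970/6,571 = 1.8.

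**Step 4. Half-widths at the plan's sizes.** 1.96 × √(P(1−P)/N), assuming independent patients.

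| Outcome | N | 95% half-width | Stated error |
|---|---|---|---|
| Recurrence, 58% | 6,394 | ±1.21 points | ±2 points |
| Recurrence, 58% | 12,000 | ±0.88 points | none stated |
| Cancer, 0.35% | 11,970 | ±0.106 points (±30%) | ±0.175 points (±50%) |
| Cancer, 0.35% | 12,000 | ±0.106 points (±30%) | none stated |

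Here 12,000 = 15,000 × 0.8. For cancer it means 42 expected events, with exact limits of about 0.25% to 0.47%.

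**Step 5. If 0.35% is an annual rate.** The 5-year risk is 1 − (1 − 0.0035)⁵ = 1.74%. With 12,000 evaluable patients that is about 209 events and a half-width of 1.96 × √(0.01738 × 0.98262 / 12,000) = 0.0023, or ±0.23 points (±13%).

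**Step 6. Could d be a detectable difference?** For a one-sample test, N = (Zα/2√(P₀(1−P₀)) + Zβ√(P₁(1−P₁)))²/d², with P₀ the plan's rate and P₁ = P₀ ± d.

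- Recurrence: 6,362 (P₁ = 60%) or 6,429 (P₁ = 56%), both close to 6,394.
- Cancer: 14,177 (P₁ = 0.525%) or 9,361 (P₁ = 0.175%), neither close to 11,970.

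**The case against.** The best defence is that d was mislabelled. The formula is a usual approximation for testing one proportion against a reference, the section speaks of detecting differences, and the literature rate could serve as that reference. For recurrence the test-based sizes nearly match. This stands as a plausible account of where the formula came from. It does not rescue the text: no reference rate is declared, d is called an error throughout, and the cancer figure does not fit such a test.

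Three other objections stand and limit the point:

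- The 2.73 factor is a normal-approximation result and overstates the excess for cancer (step 3).
- Every cancer figure depends on what 0.35% means. Section 2.3.6 introduces the 0.2% to 0.5% range as annual, the Abstract and Introduction give it without that word, and section 2.3.5 counts any cancer during follow-up.
- The half-widths assume independent patients. With 12 hospitals of about 1,000 evaluable patients each, an assumed intracluster correlation of 0.001 widens ±0.88 points to ±1.25 (0.88 × √(1 + 999 × 0.001)), and 0.005 widens it to about ±2.2, if inference extends beyond these sites.

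A reader might also infer more than the document supports:

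- That 15,000 is presented as just enough for ±2 points. It is not: the section attaches 7,993 to that error.
- That the plan misstates the precision it will deliver. It gives no such figure; the fault lies in pairing each minimum size with its error.
- That these calculations are the only basis for 15,000. The section also mentions resources and robustness of analysis, and section 2.3.10 adds expected syndrome counts.
- That 11,970 is a separate arithmetic error. It is rounding of Zβ.
- That ±0.175 points is pointless because it spans more than 0.2% to 0.5%. That range comes from the literature and is not a confidence interval to be narrowed.

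**Conclusion.** The calculation is wrong as written. The formula and the definition of d do not belong together, and nothing in section 2.3.6 turns d into a detectable difference. For the stated errors the minimum sizes are too large by a factor of 2.73 under the plan's own approximation, or by about 1.8 to 2.3 for cancer with exact limits. The cancer figures take 0.35% as the proportion affected over follow-up, as the plan's formula does.

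The error is conservative: it oversizes the study for its stated precision and harms no estimate. It does leave the power statement without support from this calculation, because no comparison was sized. The text should be corrected, but enrolment and conduct need not change.

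**What to change.** Rewrite the calculation in section 2.3.6:

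- For the estimation objective use N = Zα/2² × P(1−P)/d². Remove Zβ, the 90% power figure and the closing claims about power for differences from this calculation.
- Restate the minimum sizes: 2,340 (2,925 with loss) for recurrence. For cancer, use exact limits and name the criterion: about 5,100 if half the interval width must be within 50%, or about 6,600 if the upper limit must be.
- Say whether 0.35% is the 5-year proportion or an annual rate, and recompute the cancer size if it is annual.
- State what about 12,000 evaluable patients give, assuming independence: about ±0.9 points for recurrence and, for cancer, about ±0.11 points (±30%) around 0.35%, or about ±0.23 points (±13%) around 1.74% if the rate is annual.
- Keep 15,000 if wanted, and justify it by the association and prediction-model objectives in the Introduction.

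If a test against a reference rate was intended, the alternative is to declare that rate and call d a difference; the cancer size would then have to be recalculated.

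The cost is one rewritten paragraph. The sponsor gives up the claim that precision alone required 14,963.
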